### Trial timescales

At the current rate of patients presenting to the unit, relatively wide inclusion criteria and experience from previous trials of this nature, it is anticipated that the recruitment and treatment phase would be complete within approximately 18 months. The primary endpoint is measured at 1 year and therefore completion of data collection is anticipated in approximately 30 months (Fig. 1).

**Fig. 1 Fig1:**
[figure not shown]
Study flow chart. The total target sample size is 140, which will be randomised to endovenous laser ablation (*n* = 70) or mechanochemical ablation (*n* = 70)

### Sample size calculation

The power calculation is based upon the joint primary endpoints with 90 % power and 5 % significance. A published comparison of MOCA and radiofrequency thermal ablation found a reduction in intra-procedural pain from 35 mm to 19 mm on a 100-mm visual analogue scale (VAS) with a standard deviation of 20 mm [35]. This gives a required sample size of 33 patients per group or 73 in the trial including 10 % loss to follow-up. This difference is comparable with differences in patient-reported pain VAS, which was previously found to be associated with a difference in physical domains of quality of life and associated with changes in recovery time [8], and therefore can be judged to be clinically significant. Previous comparisons of radiofrequency ablation (RFA) with EVLA have suggested that EVLA is associated with more post-procedural pain [12, 36–38]. However older laser delivery technology (bare-tip fibres), shorter wavelength of laser (810–980 nm), additional treatment to truncal varicose vein with the allocated treatment at the same sitting, and general anaesthesia (GA) were involved; thus their findings may not be applicable today. Furthermore, no study has shown any significant benefit in quality of life relating to the reported differences.

The same study [35] reported complete target vein occlusion in 83 % of patients following MOCA at 1 month. Our previous RCT found target vein occlusion in 99 % at 1 year following EVLA [7]. A difference of this magnitude is likely to be clinically significant and have implications towards the long-term durability of the procedure, affecting effectiveness and cost-effectiveness. The required sample size to detect such a difference, if it exists, would be 62 per group or 137 including 10 % loss to follow-up. Taking this into consideration, the target sample size is 140.

### Recruitment

Each patient referred to the vascular surgery services with symptomatic SVI is assessed. Patients who potentially meet the inclusion criteria will be made aware of this research study and provided with the appropriate information, including the Patient Information Sheet. Patients expressing an interest in participation will be offered an appointment for a screening visit with a study investigator. At the screening appointment, the medical history and examination will be reviewed, followed by a detailed duplex ultrasound examination according to a set protocol based upon international consensus [39, 40]. If the potential participant meets the required inclusion criteria without any exclusion criteria, subsequent discussion of the study will take place in full (Fig. 1). If the potential participant meets the inclusion criteria for the study and is willing and able to proceed to enrolment in the trial, they will then be consented using a standardised Patient Consent Form. The Co-Investigators and Principle Investigator will obtain informed consent. Here the potential participant will be fully briefed on the trial process, the treatments, follow-up, time commitments and that this will be more detailed than regular follow-up within the non-trial setting.

To ensure confidentiality and to adhere to the Caldicott and Data Protection guidance, the participant will be assigned a unique study number for identification purposes; this will not allow identification of the study arm or any demographic information. No information identifying individuals including the study ID number will be made available to anyone outside the research group. A letter will be sent to the participant’s General Practitioner to inform them of their enrolment into the study and its details.

### Randomisation

Consented participants will be allocated to one of the two parallel treatments groups by equal randomisation (Fig. 1), which will be conducted using an online computerised service (Sealed Envelope, London, UK).

### Blinding

Due to the nature of the procedures involved it will not be possible to blind the participant or clinical team as to which group the participant is allocated. Where possible, assessor- reported outcomes will be performed by an independent assessor who is blinded to the treatment allocation. Bias in other outcomes will be limited by the use of predetermined standardised objective measurements, standardised protocols, and the extensive use of patient-reported outcomes measures.

### Data collection

Data for all outcomes from each participant’s visits will be assimilated into the participants’ unique case report form (CRF) and anonymised into a Microsoft Access database to allow further analyses, and monitored by the Research & Development (R&D) department.

### Study visits

Baseline measurements will be collected from all participants once consent is obtained and prior to randomisation. Study measurements will be taken on the day of treatment and on follow-up at 1 week, 6 weeks, 6 months and 1 year. Clinical assessment, duplex ultrasound and questionnaires are completed at these follow-up time points (Table 1).

**Table 1 Tab1:** Schedule of assessments

Visits	1	2	3	4	5	6
Procedures	Screening, eligibility, baseline assessment and randomisation	Treatment	1-week follow-up	6-week follow-up	6-month follow-up	1-year follow-up
Medication history	X	X	X	X	X	X
Medications	X	X	X	X	X	X
Physical examination	X	X	X	X	X	X
NS-SEC	X					
Employment status	X					
Informed consent	X					
CEAP	X		X	X	X	X
VCSS	X		X	X	X	X
AVVQ	X		X	X	X	X
CIVIQ-20	X		X	X	X	X
VEINES-QOL/Sym	X		X	X	X	X
SF-36	X		X	X	X	X
EQ5D	X		X	X	X	X
DUS	X		X	X	X	X
Pain VAS		X	X	X	X	X
Analgesia diary		X	X	X	X	X
Satisfaction VAS			X	X	X	X
Cosmesis VAS			X	X	X	X
Recovery time			X	X	X	X
Complications			X	X	X	X

*NS-SEC* National Statistics Socio-Economic Classification, *CEAP* Clinical severity, Etiology, Anatomy and Pathophysiology, *VCSS* Venous Clinical Severity Score, *AVVQ* Aberdeen Varicose Vein Questionnaire, *CIVIQ-20* Chronic Venous Insufficiency Questionnaire, *VEINES-QOL/Sym* VEnous INsufficiency Epidemiological and Economic Study to evaluate Quality of Life and Symptoms, *SF-36* Short Form 36-item, *EQ5D* EuroQol 5-domain utility index, DUS duplex ultrasound, *VAS* visual analogue scale

### Statistical analysis

Results will be evaluated based on an intention-to-treat analysis. Continuous data will first be tested for normality. Normally distributed data will be presented as mean and standard deviation, and hypothesis testing performed with paired and unpaired *t* tests, using two-sided significance tests with a 5 % significance threshold. If the data is not normally distributed, median and interquartile range values will be presented, with analysis using the Mann-Whitney *U* test for unrelated samples and Wilcoxon signed rank test for paired data. Categorical data will be analysed by means of *X*^2^ test or, if necessary, Fisher’s exact test. Occlusion rates will be presented as Kaplan-Meier curves, including censoring.

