### Secondary outcomes

The secondary outcomes are procedure time, post-procedural pain, analgesia use, clinical severity, generic and disease-specific quality of life (QoL), bruising, complications, satisfaction, cosmesis, time taken to return to daily activities and/or work, and cost-effectiveness analysis following EVLA or MOCA.

The procedural time is from time of starting preparation to time of finishing dressing. Post-procedural pain will be recorded on a 100-mm VAS during the first week after treatment. The type and daily dosage of any analgesia taken by patients will also be recorded in a diary for the first week. Bruising, satisfaction with treatment and cosmesis will be recorded on a separate 100-mm VAS.

Major complications include deep vein thrombosis, pulmonary embolus, stroke, loss of vision, damage to major artery, vein and/or motor nerve. Minor complications include superficial thrombophlebitis, numbness, ecchymosis, persistent tenderness, lumpiness, skin staining and wound infection.

Disease-specific QoL is evaluated using the Aberdeen Varicose Vein Questionnaire (AVVQ), the Chronic Venous disease quality of life Questionnaire (CIVIQ-20) and the VEnous INsufficiency Epidemiological and Economic Study to evaluate Quality of Life and Symptoms (VEINES-QOL/Sym). AVVQ is a validated instrument that reflects the health status impairment associated specifically with venous disease [23]. CIVIQ-20 was developed more recently and it is designed to be more patient-centred [24]. VEINES-QOL/Sym is a 26-item patient-reported disease-specific questionnaire to evaluate the QoL and symptoms across the full spectrum of conditions related to chronic venous disorders of the leg [25].

Generic QoL is assessed using the Short Form 36-item (SF-36) and EuroQol 5-domain utility index (EQ5D). The SF-36 is a multidimensional measurement of general health, which yields eight domains of functional health and well-being scores [26–28]. EQ5D is an index scale mapping three available responses to five domain questions [29], which is transformed using the UK time trade-off tariffs into a global single index scale [30]. Both have undergone extensive testing of validity and reliability, including in the context of venous insufficiency and treatment [31–33].

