Two validated objective measures will be used to assess and classify the severity of disease. The first is the Clinical severity, Etiology, Anatomy and Pathophysiology (CEAP) classification, which classifies severity into six grades. The second is the Venous Clinical Severity Score (VCSS), which grades three components from 0–3 with increasing severity, and then summates them into a single score. Clinical success is the objective improvement of clinical outcome after treatment.

Post-procedural DUS will assess the treatment efficacy [34]. Initial treatment success will be defined as complete target vein occlusion at 1 and/or 6 weeks. Anything else will be regarded as a technical failure. Recanalisation will be assessed at 52 weeks and is defined as blood flow within the target vein which has been treated. This will be broken down into partial < 25 % or full ≥ 25 % of the length of the treated vein. Residual disease is regarded as any reflux which was also present at baseline, but not a target for ablation. Disease progression will be defined as any reflux within a vein which was not present on baseline assessment. In the presence of clinical recurrence, DUS will be used to map out the pattern of the recurrence as this may give insight into techniques to avoid further recurrence and aid understanding of how recurrence comes about after these novel treatments. Post-procedural DUS will also look for evidence of complications such as heat-induced thrombosis, deep vein thrombosis, haematoma and superficial thrombophlebitis.

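### CEAP clinical class is an ordered severity grade, but the plan's only rule for categorical data is a test that ignores order, which costs power for a shift in severity

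*Protocol article*

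**What the plan says.** The Statistical analysis section sets out two families of test.

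- Continuous outcomes: "Continuous data will first be tested for normality". Those that pass get t tests, "using two-sided significance tests with a 5 % significance threshold". Those that fail get the Mann-Whitney or Wilcoxon signed rank test.
- Categorical outcomes: "Categorical data will be analysed by means of" the chi-squared test, with Fisher's exact test as the fallback.

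There is no separate rule for ordered categories. Under Secondary outcomes, clinical severity is listed: "The secondary outcomes are procedure time, post-procedural pain, analgesia use, clinical severity, generic and disease-specific quality of life (QoL"). The same section describes CEAP as a classification "which classifies severity into six grades". Table 1 (Study visits) schedules CEAP at baseline and "on follow-up at 1 week, 6 weeks, 6 months and 1 year". The second severity measure, the VCSS, is a summed score taken at the same visits.

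**The concern.** CEAP class is neither continuous nor nominal. Because the plan reserves rank tests for continuous data, the only rule that can apply to CEAP as written is the categorical one.

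A chi-squared or Fisher test on a table of grade by arm asks whether the two patterns differ in any way at all. Reordering the grades leaves the p-value unchanged. The clinical question is narrower: does one arm end up with worse grades than the other? A test that spreads its sensitivity over every possible pattern is less likely to pick up that shift than a one-degree-of-freedom test that uses the order. At stake is the sensitivity of one secondary outcome that bears on the trial's second hypothesis, that MOCA may be less effective.

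**Working it through.** **The plan's own figures.** Under Sample size calculation: "The power calculation is based upon the joint primary endpoints with 90 % power and 5 % significance". With (1.96 + 1.2816)² = 10.507:

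- Pain: 2 × 10.507 × 20² / 16² = 32.8, so 33 per group; 66 × 1.10 = 72.6, so 73 in total.
- Occlusion: 10.507 × (0.83 × 0.17 + 0.99 × 0.01) / 0.16² = 61.98, so 62 per group; 124 × 1.10 = 136.4, so 137 in total.

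Both agree with the article. It states no power for CEAP, so there is no figure to reproduce for this outcome.

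**Inputs for CEAP.** From the article: 140 patients, equal allocation, 10% loss, hence 70 × 0.9 = 63 per arm; two-sided 5%. Not in the article, so assumed: the follow-up distribution of grades, and a shift of the same odds ratio (OR) at every cut-point (proportional odds). Two distributions were used, mildest grade first:

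- A, seven levels (allowing a lowest class with no visible disease): 0.30, 0.25, 0.20, 0.08, 0.12, 0.03, 0.02
- B, six levels, matching the article's count: 0.15, 0.30, 0.35, 0.08, 0.10, 0.02

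**By hand, distribution B at OR 2.** The cumulative proportions 0.15, 0.45, 0.80, 0.88, 0.98 become 0.081, 0.290, 0.667, 0.786, 0.961 when each odds is halved. The worse arm then has q = 0.081, 0.209, 0.376, 0.119, 0.175, 0.039. The chi-squared noncentrality is

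63 × Σ (p − q)² / (p + q) = 1.29 + 1.02 + 0.06 + 0.48 + 1.29 + 0.39 = 4.54 (from unrounded values).

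The corresponding noncentrality for the rank test is also 4.54, so almost all of the signal lies in the trend. The chi-squared test must reach 11.07 on 5 df, giving approximate power 33%. The rank test must reach 3.84 on 1 df, giving 57%. The signal is the same; the loss comes from the four extra degrees of freedom.

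**Simulation.** 63 per arm; 40,000 trials per scenario for chi-squared and Wilcoxon (midranks, tie-corrected variance); 4,000 for the Fisher-Freeman-Halton test, with Monte Carlo p-values. Percentage of trials significant, shown as A / B:

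| OR | Chi-squared | Exact (Fisher type) | Wilcoxon |
|---|---|---|---|
| 1 (null) | 3.7 / 4.1 | 4.3 / 4.7 | 4.9 / 4.9 |
| 1.5 | 11 / 12 | 13 / 13 | 25 / 24 |
| 2 | 30 / 31 | 33 / 33 | 59 / 57 |
| 2.5 | 53 / 54 | 54 / 56 | 82 / 81 |
| 3 | 72 / 73 | 74 / 74 | 93 / 92 |

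The rank test holds its level under the null, so its advantage is not bought with false positives.

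**Sensitivity to the assumed distribution.** Four other shapes (spread, five grades only, concentrated in the lowest grade, six equal grades), also at 63 per arm, gave chi-squared against Wilcoxon power of 21 to 34% against 46 to 60% at OR 2, and 36 to 58% against 66 to 82% at OR 2.5. Within each shape the gap at these two odds ratios was 22 to 30 percentage points.

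**The case against.** **The assignment is inferred.** The rule is generic, sits in a condensed article, and does not name CEAP. An analysis plan that is not shown could treat ordered grades separately. This is fair and keeps the point minor. But the article does not simply stay silent: it states a rule for categorical data and confines rank tests to continuous data, and that rule fits this outcome badly.

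**Sparse grades would trigger Fisher's test.** Grades at 2% mean 63 × 0.02 = 1.3 expected patients per arm, so the exact test is the likelier one in practice. It recovers at most about 3 points, and the gap to the rank test remains.

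**The sizes are assumed.** True. The article gives neither a follow-up distribution nor an expected shift. The direction of the loss was the same in every one-directional shift tried; its size is illustrative.

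**Severity does not rest on CEAP alone.** True. The VCSS can go through the t test or Mann-Whitney route, so a directional comparison of severity is already available. A reader might infer that the plan leaves severity without one; it does not.

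**Recanalisation.** A reader might extend the point to the 52-week breakdown: "This will be broken down into partial < 25 % or full ≥ 25 % of the length of the treated vein". That does not hold as a power argument. Durability already has a binary co-primary test of complete occlusion at 1 year. With an assumed equal split of partial and full, a three-level rank test at 83% v 99% has about 95% power, and the binary test 95 to 96%. At 87% v 99% both have 83%. The breakdown is also not in the list of secondary outcomes and may be purely descriptive.

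**Conclusion.** The point holds for CEAP class and is of minor importance. As written, the plan compares an ordered severity grade with a test that ignores order. At 63 per arm and under the assumed distributions A and B, this means about 30 to 34% power instead of 56 to 59% at an odds ratio of 2, and about 53 to 57% instead of 81 to 82% at 2.5. These figures rest on assumed grade distributions and on a proportional-odds shift.

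Three stronger readings are not supported. First, an ordinal test would not reliably detect a shift: its own power is about 24 to 25% at an odds ratio of 1.5 and below 60% at 2. It is only more likely to do so. Second, reading a non-significant CEAP result as evidence of similar clinical success would be a mistake after any test, including a rank test, so it is not a consequence of this choice. Third, nothing here touches pain, 1-year occlusion or the sample size.

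**What to change.** In the Statistical analysis section, restrict the chi-squared and Fisher tests to binary and unordered categorical outcomes. Add that CEAP clinical class at each follow-up is compared between arms by one of two methods, named in advance:

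- a Wilcoxon-Mann-Whitney test with tie correction; or
- a proportional-odds model reporting a common odds ratio with 95% confidence interval, which can adjust for the baseline class already collected. This option also gives an effect size, which a rank-test p-value alone does not.

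Leave the binary 1-year occlusion test as it is. The cost is one sentence, with no new data, visits or patients. The small downside is less power against differences that do not run in one direction across the grades, which neither of the trial's stated hypotheses predicts.

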### Monitoring, safety and quality control

This study will be monitored in accordance with the Research & Development (R&D) Department’s standard operating procedures to ensure compliance with the International Conference on Harmonisation, Good Clinical Practice and the Research Governance Framework 2005.

Adverse events (AE) are defined as any untoward medical occurrence in a subject whom a medicinal product has been administered, or a procedure performed, as part of a research study, including occurrences which are not necessarily caused by or related to that investigational medicinal product (IMP). Serious adverse event (SAE) is any event if it results in death, is life-threatening, requires hospitalisation or prolongation of existing hospitalisation, results in significant or persisting disability or incapacity, and is a congenital anomaly or birth defect. Adverse reaction (AR) is any untoward or unintended response in a subjection to an IMP. Serious adverse reaction (SAR) is a serious event which is suspected (possibly, probably or definitely) to be related to an IMP and expected for the IMP. Suspected unexpected serious adverse reaction (SUSAR) is a serious event which is suspected (possibly, probably or definitely) to be related to an IMP and unexpected for the IMP, i.e. not previously documented in any of the IMP information (SmPC) or protocol.

The AE reporting period for this trial begins as soon as patients have consented to the trial and ends 30 days after the patient’s treatment visit. The health status of subjects will be checked at each study visit. The investigator will record all directly observed AE and all AE spontaneously reported by the trial subject. A pre-existing condition is a disorder present prior to the patient entering the trial and does not need to be reported as an AE unless the condition worsens or episodes increase in frequency during the AE reporting period. All AE will be followed up by investigators until the event has resolved or a decision has been taken for no further follow-up. All AE (serious and non-serious) will be recorded by the investigator in the case report forms. A description of the event, including start date, end date, action taken and the outcome will be provided.

Investigators will notify the R&D Department of any SAE within 24 hours of becoming aware of the event. The R&D Department will report fatal or life-threatening SUSARs to the Medicines and Healthcare products Regulatory Agency (MHRA) within 7 days and follow-up information in a further 8 days. The R&D Department will send all other SUSAR reports to the MHRA within a maximum of 15 days. The investigator will repot fatal or life-threatening SUSARs to the Research Ethics Committee (REC) within 7 days and follow-up information within a further 8 days. The investigator will send all other SUSAR reports to the REC within a maximum of 15 days. The investigators will submit a Development Safety Update Report (DSUR) to the MHRA 12 months after the date of the MHRA clinical trial authorisation and thereafter until the end of the study according to the MHRA website.

Participants have access to information on complaints procedure and for obtaining compensation and treatment following harm through negligence or non-negligence as a direct result of participating in the trial.

The end of trial is defined as the last visit of the last subject completing their 1-year follow-up assessment. In accordance with Trust policy all personal and/or sensitive personal data (as defined by the Data Protection Act 1998) will be securely destroyed at the conclusion of the research. Non-identifiable data and other records not containing person-identifiable data may be retained for a longer period at the discretion of the Principle Investigator. These will be stored appropriately to ensure its integrity, confidentiality and accessibility.

## Discussion

Endovenous techniques have revolutionised the treatment of truncal varicose veins, and endovenous thermal ablation has become the recommended first-line treatment method [4], achieving occlusion rates of greater than 90 % [11]. However, the search for the optimum treatment method is still ongoing and recent emphasis has focused on improving outcomes such as intra- and post-procedural pain, and reducing thermal-related injury and complications. A potential solution to the problems raised by endovenous thermal ablation is the use of newer non-thermal and non-tumescent anaesthesia treatment methods such as MOCA.

The aim of the present randomised clinical trial is twofold. The first hypothesis is that MOCA may cause less initial pain and disability, allowing a more acceptable treatment with an enhanced recovery. The second hypothesis is that this may come at a cost of decreased efficacy, which may lead to increased recurrence and affect longer term QoL, increasing the requirement for secondary procedures. In order to have sufficient power, the trial was designed using a non-inferiority principle.

In conclusion, the LAMA trial is a randomised controlled trial that aims for reduction in intra- and post-procedural pain after MOCA compared with EVLA, with a similar clinical success and technical efficacy.

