In the first human safety study, 30 great saphenous veins (GSVs) with primary SVI in 29 patients were treated with MOCA using sodium tetradecyl sulphate (STS) (Sotradecol). At 6 months [15] and at 2 years [16], the technical efficacy was 97 % (29 of 30) and 96 % (27 of 28), respectively. Several early case series have reported technical efficacy, with occlusion rates varying from 87 to 97 % [17–20]. There were no serious adverse events such as pulmonary embolism (PE), deep vein thrombosis (DVT) or nerve injury observed in all previous studies. Furthermore, prospective observational cohort studies suggest MOCA was associated with significantly less procedure times, lower post-procedural pain and faster recovery than endovenous thermal ablation techniques [21, 22]. To date, no studies have been performed to compare MOCA with EVLA in the treatment of SVI. The current study has been designed to compare MOCA with EVLA in the treatment of SVI in a randomised controlled trial (RCT).

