## Methods/Design

### Study objectives

The aim of this randomised clinical trial is to establish whether MOCA is superior to the current first-line treatment, such as EVLA. The two main hypotheses are that MOCA may cause less initial pain and disability, allowing a more acceptable treatment with an enhanced recovery. The second hypothesis is that this may come at a cost of decreased efficacy, which may lead to increased recurrence and affect longer term quality of life, increasing the requirement of secondary procedures.

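### The Discussion calls the trial non-inferiority and aims for similar efficacy, but 1-year occlusion is sized and tested for a difference, with no margin

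*Protocol article*

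**What the plan says.** All references are to the protocol article.

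- **Discussion.** The design label appears here and nowhere else: "In order to have sufficient power, the trial was designed using a non-inferiority principle". The closing sentence says the trial aims for less pain after MOCA "with a similar clinical success and technical efficacy".
- **Study objectives.** The aim is to "establish whether MOCA is superior to the current first-line treatment". On efficacy, the expectation runs the other way: "The second hypothesis is that this may come at a cost of decreased efficacy".
- **Sample size calculation.** For occlusion the planning rates are 83% for MOCA (a 1-month figure) and 99% for EVLA (a 1-year figure), with 90% power and 5% significance. "The required sample size to detect such a difference, if it exists, would be 62 per group", rising to 137 in total with 10% loss, and the target is 140. A difference of that size is described as likely to be clinically significant. No margin is given.
- **Statistical analysis.** Continuous outcomes are compared "using two-sided significance tests with a 5 % significance threshold". Categorical outcomes are compared by chi-square or, if necessary, Fisher's exact test. Both test the hypothesis of no difference.

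**The concern.** Technical efficacy at 1 year is one of two joint primary outcomes, so the framework that governs it decides what the trial may conclude. A non-inferiority design asks whether a loss as large as a stated margin can be excluded. A difference design asks whether the arms can be told apart. The two need different sample sizes and support different conclusions. In a difference design, failing to reach significance is not evidence of similarity.

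The Discussion claims the first design and says it is where the power comes from. The sample size and analysis sections describe the second. If the label and the hope of similar efficacy stay in print, a non-significant occlusion comparison could be presented as similar or non-inferior efficacy, although the trial was never sized to show that.

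**Working it through.** **1. Reproduce the stated sample size.** Inputs from the sample size section: p1 = 0.99 (EVLA), p2 = 0.83 (MOCA), 90% power, 5% significance. The two-sided difference formula with unpooled variance is

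n = (z0.975 + z0.90)² × [p1(1 − p1) + p2(1 − p2)] / (p1 − p2)²

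= (1.960 + 1.2816)² × (0.0099 + 0.1411) / 0.16² = 61.98, so 62 per group.

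This matches the plan exactly. The one-sided version of the same formula gives 50.5, so 51. The pooled versions give 66 (two-sided) and 53 (one-sided). Allowing for loss, 124/0.9 = 137.8 and 124 × 1.1 = 136.4, so the stated 137 is within rounding. The pain calculation also reproduces as a difference calculation: 2 × (1.960 + 1.2816)² × 20² / 16² = 32.8, so 33 per group.

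**2. Could 62 be a non-inferiority size?** A non-inferiority size replaces the denominator by (margin − true loss)². The true loss in the planning values is 99 − 83 = 16 points. If the margin is below 16, the planning values put MOCA beyond it. If it equals 16, the denominator is zero. No margin of 16 points or less can be powered at these rates, so 62 is not a non-inferiority figure.

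**3. What margin would the recruited number support?** The article gives no margin and no equal-rate scenario, so the rates here are assumptions. With 63 evaluable per arm (70 × 0.9), one-sided 2.5% and 90% power, the smallest margin is 3.24 × √(2p(1 − p)/63):

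- both arms 99%: about 5.7 points
- both arms 95%: about 12.6 points

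These are normal approximations with few events and are illustrative only. They show that the answer depends heavily on choices the article does not make.

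**4. How often would a real loss be non-significant?** Exact binomial calculation, 63 per arm, EVLA assumed at 99%, two-sided 5%. The article does not say when Fisher's test becomes necessary, so two rules are shown.

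| True MOCA rate | Non-significant, chi-square throughout | Non-significant, Fisher if an expected count is below 5 |
|---|---|---|
| 83% | 5% | 9% |
| 87% | 17% | 29% |
| 90% | 35% | 54% |
| 92% | 51% | 73% |
| 94% | 69% | 89% |

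The Background reports early MOCA case series "with occlusion rates varying from 87 to 97" per cent, so rates above the planned 83% are not remote. That range has no stated common time point and is not a 1-year planning range.

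**5. One possible result.** With 62 per arm, 61 occluded after EVLA and 56 after MOCA is a loss of 8.1 points. Chi-square gives p = 0.052 and Fisher p = 0.114. The Newcombe 95% CI for the loss runs from −0.6 to 18.0 points. The result is non-significant, yet the interval contains the 16-point loss that the article itself regards as likely to matter clinically.

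**The case against.** The strongest reply is that this is one mislabelled sentence in a Discussion. The objectives, outcomes, sample size and analysis sections never mention non-inferiority. They fit together as a superiority aim on pain and a two-sided test for worse occlusion, each sized by a difference calculation. That stands. A reader might infer that the article states three incompatible designs, but it does not go that far. The word superior in the objectives is loose because it is not tied to an outcome. The actual clash is between the Discussion and the sample size and analysis sections.

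It is also true that no passage says a non-significant result will be read as similarity. The closing sentence states a hope, not a decision rule. The risk of misreading is an inference from the label and that hope together.

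Finally, a journal article may leave the analysis populations and a confidence-interval rule to a fuller document, so their absence is not a defect here. The missing margin is different. The article claims a design whose sample size cannot be computed without one, and prints a calculation that has none. No fuller document could turn that printed calculation into a non-inferiority one.

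**Conclusion.** The point holds: the design statement in the Discussion is wrong as written. The sample size arithmetic is not at fault; 62 per group is correct for the difference test it describes. The errors are the non-inferiority label and the aim of similar efficacy attached to it. This should be corrected because it governs how a joint primary outcome may be interpreted.

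The practical size is the chance that a real loss goes undetected and is then called similar: about 35% to 54% at a true MOCA rate of 90%, and about 69% to 89% at 94%. These figures assume 63 evaluable per arm and EVLA at 99%, and the width of each range comes from the unstated rule for using Fisher's test.

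Two stronger readings are not supported. One is that a non-significant result would be reported as similar; the documents support only that it could be. The other is that a 9-point loss would be missed more often than not. That is so at 63 per arm under the Fisher rule (54%) but not with chi-square throughout (35%). With all 70 per arm evaluable it is 45% even under the Fisher rule.

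**What to change.** - Delete or correct the non-inferiority sentence in the Discussion, and remove the wording that presents similar technical efficacy as the aim.
- State that 1-year occlusion is a two-sided test of difference, powered for 99% against 83%.
- Report the risk difference (MOCA minus EVLA) with its 95% CI.
- Add a sentence such as: A non-significant difference in occlusion will not be interpreted as similar or non-inferior efficacy.

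Adding a non-inferiority criterion without a margin would work against deleting the claim, so none is proposed.

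The cost is a change of wording and one confidence interval, with no extra patients. The downside is that the trial's stated capability on efficacy becomes less favourable.
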